##### Qualitative data collection

It is planned to interview approximately 30 participants prior to and following the intervention, 10 from each of the three education intervention arms. The final number of participants will be determined by whether data saturation has been reached in the interviews. Data saturation will be assessed as occurring when no new information has been collected over two subsequent interviews. The pre- and post-intervention interviews will be conducted as semi-structured individual 30-min telephone interviews with practice GPs. The interview questions will be used to elicit perceptions and experiences of using MHR prior to the intervention; perceptions and experiences about the intervention; attitudes and behaviour toward rational prescribing and testing; and facilitators and barriers to achieving the expected outcomes of the educational intervention. The interviews will be audio-recorded, transcribed verbatim and coded to remove identifiers. The data collected are summarised in Table 4.

**Table 4 Tab4:** Data collection schedule

Study phase	Methods	Participants	Purpose
**Phase 1: Before education intervention**	Qualitative pre-intervention interviews	GPs approx. 30 (n=10 in each arm), approx. 30 min per interview	To ascertain perceptions and attitudes of participants before the education session intervention. • Baseline context including the use of MHR and attitudes and behaviours regarding rational prescribing and testing • Key expectations of the educational intervention • Anticipated outcomes of the intervention • Expected facilitators of, and barriers to, achieving the expected outcomes
	Quantitative pre-intervention audit of rates of specified prescribing, pathology and imaging ordering and MHR access for 6 months prior to the intervention	GPs n=40 in each arm, automated de-identified data extraction	To describe baseline rates of selected prescribing, pathology and imaging
	Pre-intervention survey with case scenarios to test intention to prescribe/order and use of MHR	GPs n=40 in each arm, approx. 30 min per participant	To describe baseline knowledge and skills
	Quantitative project uptake data	GPs n=40 in each arm, automated data extraction	To assess GP engagement with the intervention module completions, webinar attendances and site logins will be collected by Medcast.
**Phase 2: After completion of education intervention**	Post-intervention knowledge assessment with case scenarios to test intention to prescribe/order and use of MHR	GPs n=40 in each arm, approx. 30 min per participant	To describe changes from baseline between arms in knowledge and skills
	Qualitative post-intervention interviews	GPs approx. 30 (n=10 in each arm), approx. 30 min per interview	To ascertain perceptions and attitudes of the participants after the education session intervention. • Post-intervention context including use of MHR and attitudes and behaviours regarding rational prescribing and testing • The degree to which key expectations of the educational intervention were met • The degree to which the anticipated outcomes of the intervention were met • Facilitators of, and barriers to, achieving the expected outcomes • What worked for whom, where and why?
	Quantitative Post-intervention audit of rates of selected prescribing, pathology and imaging ordering	GPs n=40 in each arm, automated de-identified data extraction	To describe changes from baseline rates of selected prescribing, pathology and imaging between arms of the trial
	Mixed methods synthesis	All	Synthesis and analysis to provide in-depth evaluation of the project.

### Plans to promote participant retention and complete follow-up {18b}

Once enrolled in the education programme, participants will receive the standard prompts and reminders regarding education activities that would normally occur when enrolled in an equivalent programme under non-trial conditions (outlined in Section 11C).

### Data management {19}

The UOW research team has created a Data Management Plan which addresses the separation of Medcast from data collection and analysis. Three data repositories will be established in CloudStor, a secure encrypted UOW approved cloud storage resource with secure password-only access and servers based in Australia. This will facilitate the separation of data from master code sheets and provide access to only those members of the research team who require access to the data. As part of this Data Management Plan, the Medcast team will only have access to the following data:
GP knowledge Quiz dataProject uptake data

Repository 1 will be shared between Medcast and UOW research team members. Coded knowledge quiz data will be stored in Repository 1 by Medcast. Following the intervention period, Medcast access to Repository 1 will be withdrawn. Repository 2 will be used to store the master coding sheet which links the GP participants’ identifying information to a six-digit study ID (coding the practice and the individual participant). This repository will also be used to store the randomisation allocation list. This repository will be kept separately and accessible only to the UOW Principal Investigator and project officer. Repository 3 will contain the coded, de-identified clinical audit electronic health record data. Via the PenCS software, de-identified electronic health record audit data will be transferred from the practices, coded by the participating clinician’s study ID, directly into this repository. This repository will also hold the coded, de-identified qualitative interview audio files and transcripts. This repository will be accessible only to the UOW research team members.

CloudStor, the cloud data platform to be used in the project, is administered by AARNet. UOW is a member of AARNet and CloudStor is a UOW approved research data storage option. CloudStor servers are located in Australia and data stored in CloudStor are encrypted and password protected. Ongoing access to the data will be limited to the UOW research team members involved in analysis and publications.

Hard copies of all consent forms will be stored in a locked filing cabinet in the Department of General Practice at UOW, or password-protected folder on CloudStor if in soft copy form. All data will be kept in accordance with UOW research data policies, stored for 5 years and thereafter permanently deleted.

### Confidentiality {27}

In order to maintain confidentiality and privacy, the researchers will establish secure data storage and management procedures.

A digital record of consenting GPs and practices will be available to Medcast and PenCS by the UOW research team by secure internet file transfer. This is needed as the Medcast research team requires access to identifying information of GPs and practices and identifiable participant knowledge quiz data in order to implement the education intervention and administer the professional development requirements, and PenCS requires identifying information of GPs and practices to perform the data extraction.

The UOW research team will allocate a six-digit study identifier to each consenting GP. The identifying information of the GPs and their study ID will be stored on a coding master-sheet kept securely and separately from all other study data.

The unit-level data from each practice is de-identified on-site by the PenCS software and coded according to the consenting GP generating the data. Only data generated by consenting GPs will be extracted.

The de-identified practice data will be transferred securely directly from the practice server to a secure UOW data repository (as is described in further detail below). Therefore, there is no risk that the data is at risk between points, as it is sent directly to UOW and not housed anywhere but the practice server and the UOW secure data repository.

All qualitative interviews will be digitally recorded and coded, then de-identified by the professional transcription service. Once quality checking of the coded audio files has been performed, the original audio files will be deleted. Participants can request removal of their identifying data at any time, and any re-identifiable data up until analysis is complete.

### Plans for collection, laboratory evaluation and storage of biological specimens for genetic or molecular analysis in this trial/future use {33}

No laboratory or biological specimens will be collected as part of this research.

### Statistical methods

#### Statistical methods for primary and secondary outcomes {20a}

The use of a randomised recruitment design and stratified randomisation of the intervention will reduce the potential for sampling bias. The statisticians will be blinded as to participant groups for analysis. Each of the data elements will be statistically analysed using linear mixed models test for between-group (intervention versus control) differences in the change in variables over the course of the study period accounting for any clustering. Where appropriate, analyses will control for demographic (age and sex) and practice environment (size, area-level socioeconomic disadvantage and rurality) variables and include MHR access rates as a covariate (the pre/post-evaluation of uploads of the MHR shared health summary).

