### Rationale for extending phase I into phase II

This pragmatic trial is an extension of a pilot study (phase I) which reported promising outcomes from MHR educational intervention (ethics approval 2018/047) [34]. Phase I indicated that the intervention and use of MHR in clinical practice, based on general practitioner (GP) responses around intention-to-treat, demonstrated knowledge, skill and attitude changes among GP study participants with regards to evidence-based de-prescribing and ordering of pathology and diagnostic imaging tests. Phase I also demonstrated uptake of an ‘is this needed’ step in participants’ clinical reasoning and increased attention to reducing unnecessary healthcare expenditure. GPs reported, post-intervention, that they were more motivated to use MHR and were checking it more often, as well as feeling more confident about using it. In addition, there were significant behaviour changes regarding deprescribing. In particular, GPs reported that they discussed de-prescribing with patients more often, reduced rates of prescribing fluticasone (inhaled corticosteroid) and reduced prescribing of metformin and paracetamol/codeine combinations (among a subset of participants). There was also a significant reduction in test ordering for full blood count (FBC) and liver function tests (LFTs) from pre-intervention to post-intervention. The economic impact measured as part of the intervention indicated the potential for significant cost savings to the health system. Phase I however was limited by the following factors:
Small sample size;Lack of controls for the educational components;Inability to access real-world outcomes to measure changes in clinician behaviour (using quantitative data) over time;Resultant restrictions on health economics analysis.

The current phase II study is designed to overcome the limitations of phase I.

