### Interventions

#### Explanation for the choice of comparators {6b}

Trial participants will be randomised to one of three parallel arms. Each arm will receive different topic content for prescribing, pathology ordering or imaging ordering as a standardised education process intervention. Each arm will act as controls for each other, for example, participants in the pathology arm will act as controls for the imaging and prescribing arms; participants in the imaging arm will act as controls for the pathology and prescribing arms; and participants in the prescribing arm will act as controls for the imaging and pathology arms. In this manner, the change in clinician behaviour associated with the education intervention for a given topic content arm can be compared against clinicians receiving the equivalent education process exposure but for different topic content in the other two arms.

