##### Intervention

Medcast Pty Ltd. will develop and implement the education intervention which will focus on three topic streams running in parallel. The topic streams include a rational prescribing education intervention, a rational pathology-ordering education intervention and a rational diagnostic-imaging education intervention. All three topic streams will be in the context of the use of MHR in achieving quality improvement (QI) benefits and in integrating MHR into clinical practice. The ‘Choosing Wisely’ recommendations [5], an initiative of the National Prescribing Service Australia, will inform the education content, along with other sources of current evidence-based practice [6–11]. The Choosing Wisely recommendations, which are evidence-based, are supplied and endorsed by every peak medical and nursing body in Australia. The prescriptions and tests included in the study are specified a priori for the education sessions and then assessment. These same tests and prescriptions are assessed across all three arms of the trial 6 months pre- and post-intervention. The intervention pathology tests, imaging tests and prescription medication were chosen based on their frequency in general practice, cost to the PBS and potential for adverse outcomes in patients [13, 15, 16, 37].

Each GP participant will be required to complete pre- and post-intervention assessments for all of the prescribing, pathology and imaging educational domains, as although participants are randomised into one arm of the trial, the other two arms act as controls. This will allow assessment of the knowledge and skills acquisition of the GP participants, attributable to the arm of the intervention they have been randomised into, in comparison with the other arms. See Fig. 2 for a comparison of the educational activities in each arm.

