**Online learning module (60 min)**	
To include data of national, current trends in inappropriate prescribing and testing ordering, as relevant to each arm of the study.	
Information about MHR, the future of MHR and current uptake.	
Tips and tricks for engagement, barriers, algorithms that can be used.	
Information about where MHR can fit into practice—checking the record, look for duplicates, identifying medications prescribed or test results from elsewhere.	
A case study scenario demonstrating using MHR.	
Relevant case studies will be incorporated to apply the information delivered in the module.	

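### The optional MHR covariate includes uploads recorded after randomisation, which could bias the between-arm contrast if topic content moves uploads differently by arm

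*Protocol article*

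**What the plan says.** All points are in the Protocol article.

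- **Model.** Statistical methods for primary and secondary outcomes {20a} describes the analysis as "linear mixed models test for between-group (intervention versus control) differences in the change in variables over the course of the study period". Section {20b} carries the same method into subgroup analyses.
- **Covariates.** The relevant sentence in {20a} is conditional: "Where appropriate, analyses will control for demographic (age and sex) and practice environment". It goes on to say that analyses will "include MHR access rates as a covariate (the pre/post-evaluation of uploads of the MHR shared health summary".
- **MHR in the education.** Intervention {11a} states: "All three topic streams will be in the context of the use of MHR". The online module in Table 2 covers how the record can be used in practice, including to "look for duplicates, identifying medications prescribed or test results from elsewhere".
- **Comparator.** Section {6b} compares each topic arm with "clinicians receiving the equivalent education process exposure but for different topic content in the other two arms".
- **Pilot.** The rationale for phase II reports that "GPs reported, post-intervention, that they were more motivated to use MHR and were checking it more often".
- **Analysis principle.** Section {20c} commits to intention-to-treat.

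**The concern.** Age, sex, practice size, area disadvantage and rurality are fixed before the education starts. The MHR measure is different, because its post-intervention part is observed after randomisation and after teaching that encourages MHR use. The background section also presents MHR to participants as an aid to reviewing medicines and tests, so the protocol itself describes a route from MHR behaviour to the ordering outcomes.

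Conditioning on such a variable can do two things. If it lies on the path from assignment to outcome, the arm coefficient becomes a direct effect with that route taken out. If it only shares causes with the outcome (a generally engaged GP may both upload more and order less), conditioning can bring confounding into a comparison that randomisation had kept clean. Either would matter for a trial whose stated objective is the effect of education in the context of MHR.

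There is also a naming problem. The covariate is called access but defined by uploads, whereas the behaviour taught is mainly checking the record.

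**Working it through.** **1. Is the covariate post-randomisation?** In part, yes. Whether it enters as a change score, as separate pre and post values, or as a time-varying value in a long-format mixed model, a pre/post measure brings post-intervention data into the model.

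**2. Is a between-arm difference in uploads built into the design?** No. MHR content goes to every arm and the randomised contrast is topic. A difference is possible, however. In Table 2 the case studies, national trend data, clinical audit, case templates and case-based webinars are specific to the arm, and these could lead to different MHR activity.

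**3. Effect scale.** The plan gives no figure for this covariate, so I use the effect in its sample size section, f² = 0.15. The stated size reproduces: with one tested predictor, N = 55, noncentrality 0.15 × 55 = 8.25 and 1 and 53 degrees of freedom, power is 0.805, and 55 is the smallest N reaching 0.80. With equal allocation, f² = d²/4, so d = 2 × √0.15 = 0.775 SD.

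**4. Mediation.** Let τ be the total effect (-0.775 SD), a the between-arm difference in upload change (SD), and b the effect of uploads on the outcome change. Neither a nor b is in the document; both are assumptions.

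Adjusted arm coefficient = τ − a·b; share removed = a·b/τ.

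Each row was also simulated (40 against 80 GPs, no clustering, 3,000 replicates):

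| a | b | a·b/τ | Simulated unadjusted | Simulated adjusted | Removed |
|---|---|---|---|---|---|
| 0 | -0.2 | 0% | -0.765 | -0.765 | about 0% |
| 0 | -0.4 | 0% | -0.771 | -0.771 | about 0% |
| 0.2 | -0.2 | 0.04/0.775 = 5.2% | -0.772 | -0.732 | 5.1% |
| 0.2 | -0.4 | 0.08/0.775 = 10.3% | -0.776 | -0.696 | 10.4% |
| 0.5 | -0.2 | 0.10/0.775 = 12.9% | -0.777 | -0.677 | 12.8% |
| 0.5 | -0.4 | 0.20/0.775 = 25.8% | -0.771 | -0.572 | 25.8% |

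**5. Common cause only.** Uploads were given no effect on the outcome, but an unmeasured factor was given loading 0.5 on uploads and -0.5 on the outcome. With a = 0 the estimate is unchanged (-0.778 and -0.777). With a = 0.5 it moves from -0.778 to -0.656, a shift of 0.122, or about 16%.

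**6. Direction.** The shift depends on the sign of a·b. Each topic arm is compared with the other two. If mᵢ is the mean upload change in arm i and arms are equal in size, aᵢ = mᵢ − (mⱼ + mₖ)/2, and the three values sum to zero. If uploads relate to ordering with the same sign for all three topics, an effect understated for one topic must be overstated for at least one other. The adjustment therefore has no single predictable direction.

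**The case against.** The strongest objection is that MHR teaching is common to all arms. A behaviour promoted equally everywhere is not, by design, on the path from topic assignment to outcome, and the Limitations section says openly that there is no arm without MHR. This stands: at a = 0 neither mediation nor a common cause moves the estimate. A reader might infer from the covariate sentence that part of the intervention effect is removed, or that randomisation no longer protects the comparison. The documents do not support either as a stated fact, because both need upload change to differ by topic arm and nothing in the article says that it does.

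Three further points also limit the concern:

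- Uploads are probably a weak proxy for checking the record, and no section explains how uploading a summary would reduce the same GP's ordering. Any mediated share through uploads may be small.
- The pilot result is self-reported checking, not uploads. The article lists the lack of controls for the educational components among the pilot's limits, so it says nothing about differences between topics.
- The adjustment is qualified, and the exact form of entry may be set out in an analysis plan that is not shown.

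The qualifier does not settle the matter. It leaves a covariate that may respond to assignment available for the main models, to be decided later, while the covariate's definition already includes post-intervention data.

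Table 4 names MHR access only in the pre-intervention audit; the later row reads "Quantitative Post-intervention audit of rates of selected prescribing, pathology and imaging ordering". Taken literally, only baseline MHR data would exist and the concern would fall away. But {20a} and the Limitations section both describe a pre/post assessment, so this is more likely a shortened table row. The passages should be reconciled; little should be built on the difference.

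**Conclusion.** The point holds in conditional form. The protocol permits the primary and secondary models to adjust for a variable that is partly post-randomisation and belongs to a behaviour domain the education addresses. If upload change is equal across arms, the adjustment does no harm to the contrast. If it differs, the arm coefficient is no longer the effect of assignment that intention-to-treat implies, although the data-inclusion rule in {20c} is still met.

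The size cannot be derived from the document. The 5% to 26% range rests entirely on assumed values of a (0.2 to 0.5 SD) and b (-0.2 to -0.4), and the 16% figure on assumed common-cause loadings. They show how the bias would behave and do not predict its size in this trial. The sign is also open. The stated sample size is unaffected: allowing for one or two further predictors in the model, the calculation still returns 55. This is an avoidable bias risk that is worth correcting, but not a flaw that by itself invalidates the planned comparison.

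**What to change.** Amend the covariate sentence in {20a} so that:

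1. the only MHR covariate in the primary and secondary models, and in the subgroup models that inherit the method, is the upload rate in the 6 months before the intervention, or no MHR covariate is used;
2. post-intervention uploads are analysed as a separate outcome by arm, or in a mediation analysis labelled exploratory;
3. the measure is called shared health summary uploads rather than access, and Table 4 is brought into line with {20a} on when it is collected.

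The cost is one sentence and a table entry. No extra data are needed, since {20a} already plans a pre/post measure, and recruitment is unaffected. The only possible loss is some precision if post-intervention uploads would have explained more outcome variance than the baseline rate; the document gives no basis for putting a figure on that.

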#### Interim analyses {21b}

As this is an educational intervention, no interim analyses will be performed.

#### Methods for additional analyses (e.g. subgroup analyses) {20b}

The method for subgroup analyses will be the same as those for the primary analysis.

